### Research questions (RQs)

***(RQi)*** Is the SP pathway for youth reporting low community connection or loneliness feasible, acceptable and suitable to stakeholders?

***(RQii)*** Is the study design, including measurement framework, feasible, acceptable and suitable to stakeholders?

***(RQiii)*** Are the assumptions in the power calculation (specifically the intraclass correlation coefficients) realistic to allow for adequate power to be able to test for differences?

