Finally, a subsample of YP (n =  24) and stakeholders (n =  18) in the intervention arm will be asked to take part in a qualitative interview to better understand the feasibility and acceptability of the SP pathway, as well as barriers and facilitators to engagement and implementation. Topic guides are shown in the S1 and S2 Files. Purposive sampling will be employed. For YP, purposive sampling will take into account socio-demographic factors, such as age, gender, ethnicity, site, loneliness score, and the degree to which they engaged in SP (none, some, a lot). For LWs and school staff, purposive sampling will take into account sociodemographic factors, location, role, and types of activities prescribed (for LWs). The number of interviews has been selected to be large enough to allow for adequate “information power” and to make meaningful comparisons between social prescribing pathway delivery and experiences in different sites [33] but not too large to dilute an in-depth rich analysis and exploration of individual participant accounts.

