
### Data analysis

***(Rqi)*** To assess the feasibility, acceptability and suitability of the SP pathway, descriptive statistics will be calculated from stakeholders’ questionnaire data responses, how many YP take up the SP offer, as well as via qualitative interview data which will be analysed using framework analysis [51] a method which allows for both deductive and inductive coding of transcripts across multiple stakeholder accounts.

***(Rqii)*** To assess the feasibility, acceptability and suitability of the study design, descriptive statistics will be calculated exploring measure completion rates, as well as from interview data using framework analysis [51].

Implementation data will be used to determine whether pathway refinements are needed and outcome measures will inform refinements to sample size (establishing ICCs and effect size). Crucially, the project will not proceed to full trial until pre-established “stop-go” criteria have been met (see Table 1). If the criteria are partially met, the research team will further develop trial plans (e.g., tweaking the SP pathway, reducing the number of follow-up measures, etc). This will be signed off by the Trial Steering Committee (TSC) prior to proceeding to full trial.

**Table 1 pone.0317823.t001:** Stop-go criteria.

Method	Indicator	Fully met (proceed)	Partially met (proceed with amendments agreed by TSC)	Not met (stop)
Acceptability of intervention	Qualitative reports of acceptability from young people, school staff and link workers	The majority (>50%) of stakeholders report the social prescribing intervention is acceptable	Some stakeholders report the social prescribing intervention is not acceptable but identify alterations that need to occur	The majority (>50%) of stakeholders report the social prescribing intervention is not acceptable even with modifications
	Proportion of young people attending an appointment with a link worker	55-100%	40-54%	0-39%
Acceptability of evaluation framework	Qualitative reports of acceptability from young people, school staff and link workers	The majority (>50%) of stakeholders report the social prescribing intervention is acceptable	Some stakeholders report the social prescribing intervention is not acceptable but identify alterations that need to occur	The majority (>50%) of stakeholders report the social prescribing intervention is not acceptable even with modifications
	Proportion of young people completing baseline measures	55-100%	40-54%	0-39%

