Ability to collect 3-month data from pupils who completed baseline measures	Proportion of young people completing 3 month follow up	55-100%	40-54%	0-39%
Negative consequences of the intervention	Reported negative/adverse effects of social prescribing from young people, school staff or link workers	No evidence of substantially negative effects on young people	–	Evidence of substantially negative effects on young people

***(Rqiii)*** To assess whether power calculation assumptions are realistic, descriptive statistics, and point estimates of the within-person intraclass correlation coefficients (ICCs) for all instruments based on the pilot data will be calculated, as well as a bootstrap study exploring the upper bounds for the ICCs.

Where questionnaire data is missing from participants at random, multiple imputation will be employed. There will be no interim analysis given the short timescale (6 months) that participants are involved in the intervention.

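### Table 1's qualitative stop-go criteria for the evaluation framework repeat the intervention criteria, so they cannot show whether stakeholders accept the study design or measures

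*Protocol article*

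**What the plan says.** The second research question asks: "Is the study design, including measurement framework, feasible, acceptable and suitable to stakeholders"? Under Data analysis, it is to be answered from measure completion rates and from interview data.

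Table 1 in the same section sets the criteria that must be met before a full trial. If they are only partly met, plans are developed further and signed off by the Trial Steering Committee. Two rows carry a qualitative indicator, one for the intervention and one labelled "Acceptability of evaluation framework". The cells of the second are:

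- fully met: "The majority (>50%) of stakeholders report the social prescribing intervention is acceptable"
- partially met: "Some stakeholders report the social prescribing intervention is not acceptable but identify alterations that need to occur"
- not met: "The majority (>50%) of stakeholders report the social prescribing intervention is not acceptable even with modifications"

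The evaluation-framework row also has a numerical indicator, "Proportion of young people completing baseline measures". The next row is headed "Ability to collect 3-month data from pupils who completed baseline measures". Both use bands of 55-100%, 40-54% and 0-39%.

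Under Participants, 24 young people and 18 stakeholders "in the intervention arm will be asked to take part in a qualitative interview". The stated aim is to understand the social prescribing pathway.

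**The concern.** The label and the criteria refer to different things. The row is meant to judge the evaluation framework, but its qualitative cells judge the intervention. Because progression to a full trial depends on this table, the mismatch is in a decision rule and not in descriptive text.

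The case that matters is one where stakeholders like social prescribing but object to the trial around it: being randomised, receiving a leaflet as the comparator, or the length of the surveys. As written, the qualitative indicator would be recorded as fully met. The plan itself anticipates this kind of problem, since it lists cutting the number of follow-up measures as a possible amendment. Yet no qualitative cell asks about the measures.

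**Working it through.** **1. The two qualitative rows side by side.** In both rows the fully met, partially met and not met cells are identical, and each names the social prescribing intervention. None mentions randomisation, the comparator, the questionnaires or follow-up.

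**2. What the duplicate row can return.** It applies the same words to the same interviews, so its result always equals that of the intervention row.

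| Stakeholders' view of the intervention | Their view of the design and measures | Intervention row | Evaluation row as written | Evaluation row as labelled |
|---|---|---|---|---|
| accept | accept | met | met | met |
| accept | reject | met | met | **not met** |
| reject | accept | not met | not met | **met** |
| reject | reject | not met | not met | not met |

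The evaluation row is mis-scored in the second and third cases. In the third, the overall decision does not change, because the intervention row already stops the project. Only the second case can alter progression.

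**3. What else gates the second research question.** Three indicators bear on it:

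- the qualitative cells, which name the wrong object;
- baseline completion, which works as written;
- 3-month completion, which works as written. The Procedure section follows up pupils in both arms.

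**4. How far the completion rates fill the gap.** Baseline surveys come before allocation (Procedure), so that rate says nothing about randomisation or signposting.

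For the 3-month rate, take the pilot sample under Participants: 780 × 0.14 × 0.71 = 77.5, which agrees with the stated figure of about 78 (39 per arm). Assume that the gate is applied to these 78 pupils with both arms pooled; Table 1 states no per-arm rule.

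- Needed for the top band: 0.55 × 78 = 42.9, so 43 pupils.
- If all 39 intervention pupils respond, the controls needed are 43 − 39 = 4, and 4/39 = 10%.

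This is the extreme case, not a forecast. It shows that a pooled completion rate can pass while the control condition is largely abandoned. Follow-up also carries a £10 voucher, so completing a survey is not the same as finding it acceptable.

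**5. Survey burden.** Adding the item counts under Study outcome measures for baseline:

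- Primary: 3 + 12 + 6 + 10 + 11 + 4 + 5 + 3 + 11 + 4 + 3 + 4 + 4 = 80 items.
- Secondary, adding stress (4) and flow (13): 80 + 17 = 97 items.

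Acceptability of the measures is therefore a real question for pupils aged 9 to 13.

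**6. Who is interviewed.** Planned interviews total 24 + 18 = 42, so more than 50% means at least 22 if all are pooled. The pupils are placed in the intervention arm, sampled partly on how far they engaged with social prescribing, and interviewed at least 3 months after receiving it. On that description none of the 24 comes from the signposting arm, which is 39 of the 78 pupils.

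**The case against.** The strongest reply is that this is a copying error with limited consequences. The row label and the research question make the intended object plain, and the full protocol (V1.0) is not shown, so the slip may exist only in the article. That is plausible, but the published rule is still wrong as it stands. Topic guides that ask about the design, which are in supplementary files not shown, would not repair a decision cell that names something else.

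A reader might also draw stronger conclusions, which the documents do not support:

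- *That the gate for the second research question never tests the study design.* Baseline and 3-month completion are numerical stop-go tests of it, and completion rates are a stated part of that analysis. They are also a direct, if partial, measure of survey burden.
- *That control pupils and those who deliver signposting are never asked anything.* Under Procedure, follow-up surveys for both groups include questions on what pupils thought of the intervention. Under Participants, staff involved in signposting complete a feasibility, acceptability and suitability survey. Randomisation is by pupil, so staff have no arm, and interviewed staff may have seen both conditions. None of these sources feeds the qualitative cell in its present wording.
- *That a sound design could be stopped because the intervention was disliked.* The intervention row would stop the project on the same answers, so the duplicate adds no further stop.
- *That 24 interviews from 39 intervention pupils (24/39 = 62%) is itself a fault.* The article gives no expected opt-in rate, so the figure does not show that purposive sampling will fail.

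Interviewing control pupils is a trade-off. The article justifies the number of interviews by information power and comparison between sites, and every interview moved to the control arm reduces depth in the intervention arm.

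**Conclusion.** The point holds for the qualitative criteria. One of the three indicators bearing on the second research question cannot detect rejection of the design or measures, because all three of its cells name the intervention. Only completion rates then gate that question, and the row's qualitative part could be scored as fully met for a design that stakeholders find unacceptable. Such a design would still have to pass the baseline and 3-month completion thresholds before proceeding.

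The correction is needed because progression depends on this table. The core of the point rests on the wording alone and on no numerical assumption. The 4-of-39 illustration rests on a pooled 3-month rate among 78 pupils. The lack of control-pupil interviews is secondary: it limits what the interviews can say about the design, but it does not by itself invalidate the plan.

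**What to change.** **Required.** Reword the three qualitative cells of the evaluation-framework row so that their object is the evaluation framework: being randomised, having signposting as the control, and the content and length of the baseline, 3-month and 6-month surveys. The existing structure can stay: majority acceptable; some not acceptable but with changes identified; majority not acceptable even with modifications. The cost is three table cells and a check that the topic guides contain questions to inform them. If the full protocol already has the right wording, the article alone needs correcting.

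**Optional.** Either include some signposting-arm pupils within the existing 24 interviews, or state that the qualitative conclusion about the study design applies to intervention-arm pupils and staff only. The first means fewer intervention-arm interviews. The second costs one sentence but leaves control pupils' views of the design outside the qualitative evidence.

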## Materials and methods

### Design

This manuscript relates to the INACT pilot study protocol V1.0 05-02-24 and follows the SPIRIT checklist (see S1 Checklist). Any details of protocol amendments will be submitted to the journal after approval from UCL ethics committee. INACT will adopt a two-group (intervention vs. active control) parallel randomised design, with YP as the unit of randomisation. YP allocated to the intervention arm will receive SP, while those in the control arm will receive signposting from school staff to activities in their local area. Outcomes will be assessed at baseline (T0), 3 months after being allocated to SP or signposting (T1), and 6 months after being allocated to SP or signposting (T2).

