### Participants

We aim to recruit a total of 12 schools (6 primary schools and 6 secondary schools). In each primary school, one class from each of Years 4 and 5 (children aged 9 and 10 years old) will be selected, whilst in secondary schools, two classes each from Years 7 and 8 (children aged 12 and 13 years old) will be selected. Year 6 (children aged 11 years old) will be excluded from taking part because previous studies by the research team have shown that schools are reluctant to engage Year 6 students in research due to exam preparation [30,31]. Private schools will be excluded because they have greater resource to support YP with wellbeing difficulties and do not use unique pupil numbers linked to the National Pupil Database, which will be needed to explore factors associated with low community connection and loneliness.

Approximately 780 pupils (exact number dependant on class size) will complete baseline surveys to examine the prevalence rates of low community connection and loneliness and factors that predict this. Under realistic assumptions from other trials [31] and reviews on low community connection and loneliness [14] (low community connection/loneliness prevalence =  14%, participation rate =  71%), approximately 78 pupils will participate in the pilot study (39 receiving SP and 39 receiving signposting). YP eligible for the pilot study will be those reporting feelings of loneliness (≥6) using the 3 loneliness questions from the Good Childhood Index [32]. This corresponds to YP who report feeling lonely at least some of the time across all three questions. YP who are persistently absent from school will be included. YP reporting severe learning disability will be excluded.

In addition to YP, approximately 20 other stakeholders, namely LWs and school pastoral staff, will participate in the pilot study. Pre-intervention, a single member of staff in each participating school will be asked to complete a school wellbeing provision survey. Typically, this will be the named mental health lead; in schools where there is no named mental health lead, it may be the member of staff with primary responsibility for personal, social and health education (PSHE) provision or pastoral support. Post-intervention, school staff who were involved in signposting and LWs who provided SP will be asked to complete a feasibility, acceptability and suitability survey.

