#### Study outcome measures.

The proposed primary outcome measure for INACT is the 3 loneliness questions from the Good Childhood Index [32]. Each question is scored on a three-point Likert scale ranging from 1 ‘hardly ever or never’ to 3 ‘often’. Higher total scores indicate higher levels of loneliness. This is assessed at baseline, 3 and 6 months. The primary timepoint is at 3 month follow up.

Secondary measures were chosen with young person and subject expert input. These include:

*For young people*

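### RQiii explores only the upper bound of the within-person ICC, which is the favourable bound for sample size under a baseline-adjusted or change-score analysis at 3 months; the cautious lower bound is not planned

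*Protocol article*

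**What the plan says.** Under Research questions, RQiii asks whether the assumptions of the power calculation hold, "specifically the intraclass correlation coefficients". Data analysis answers it with descriptive statistics, "point estimates of the within-person intraclass correlation coefficients (ICCs) for all instruments", and a bootstrap: "as well as a bootstrap study exploring the upper bounds for the ICCs". The same section says that outcome data will be used to refine the sample size through ICCs and an effect size.

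Three design features decide how a within-person ICC acts on sample size. The Design section describes a "parallel randomised design, with YP as the unit of randomisation". The primary outcome, the three-item loneliness score, is measured at baseline, 3 and 6 months. Of the follow-ups, one is primary: "The primary timepoint is at 3 month follow up".

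The Procedure section adds that link workers see only pupils allocated to the intervention arm. The within-person ICC is the only type the article names.

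**The concern.** An upper bound is the cautious choice for a clustering ICC, where more correlation means more variance. A within-person ICC usually acts the other way in a trial with a baseline measure and one primary follow-up: the better the baseline predicts the outcome, the fewer pupils are needed. Stress-testing the assumption at the upper bound then examines only the case in which the full trial can be smaller. The unfavourable case, a weaker correlation than assumed, is not examined.

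Informing the full-trial sample size is one of the three stated aims of the pilot. A check that looks only in the favourable direction can endorse a power calculation that is too optimistic.

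There is a related gap. Pupils in the social prescribing arm who share a link worker may have correlated outcomes, while control pupils have no link worker. This clustering would inflate the variance in one arm, and a within-person ICC does not measure it.

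**Working it through.** **The article's own figure.** The Participants section gives "Approximately 780 pupils (exact number dependant on class size) will complete baseline surveys", a prevalence of 14% and a participation rate of 71%. 780 × 0.14 × 0.71 = 77.5, which reproduces "approximately 78 pupils will participate in the pilot study (39 receiving SP and 39 receiving signposting"). This is a recruitment yield. The full-trial power calculation is not shown, so its effect size, power and assumed ICC are unknown.

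**Direction.** Take equal variances and a common correlation r between waves. Relative to an unadjusted comparison at one timepoint, the required n is multiplied by:

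| Analysis | Factor | As r rises |
|---|---|---|
| 3 months, unadjusted | 1 | no change |
| 3 months, baseline-adjusted | 1 − r² | falls |
| 3 months, change score | 2(1 − r) | falls |
| Mean of 3 and 6 months, unadjusted | (1 + r)/2 | rises |
| Mean of 3 and 6 months, baseline-adjusted | (1 + r)/2 − r² | rises below r = 0.25, falls above |

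The turning point in the last row comes from setting the derivative ½ − 2r to zero.

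**Size, for the baseline-adjusted 3-month analysis.** Assumed, not in the article: r = 0.5, two-sided 5% level, 90% nominal power. The Fisher z interval, tanh(atanh(r) ± 1.96/√(n − 3)), stands in for the bootstrap.

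- With 78 pairs: atanh(0.5) = 0.549 and 1.96/√75 = 0.226, so the interval is 0.31 to 0.65.
- 1 − r² is 0.903 at the lower bound, 0.750 at the point estimate and 0.577 at the upper bound.
- n at the upper bound relative to the point estimate: 0.577/0.750 = 0.77. Relative to the lower bound: 0.577/0.903 = 0.64.
- Power if sized at the upper bound is Φ((1.96 + 1.2816)·√ratio − 1.96), which gives 81% if r = 0.5 and 74% if r = 0.31.
- At 55% follow-up, the lowest 3-month completion that Table 1 counts as fully met, 0.55 × 78 ≈ 43 pairs. The interval is 0.23 to 0.70 and the two powers are 77% and 67%.
- Change scores with 78 pairs: 77% and 64%. Mean of both follow-ups with baseline adjustment: 83% and 79%.

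**Other values of r.** n per arm from 78 pairs, assuming a standardised effect of 0.3 and 80% power (175 per arm before adjustment):

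| r | 95% interval | n at lower bound | n at point estimate | n at upper bound |
|---|---|---|---|---|
| 0.3 | 0.08 to 0.49 | 174 | 160 | 134 |
| 0.5 | 0.31 to 0.65 | 158 | 132 | 102 |
| 0.6 | 0.44 to 0.73 | 142 | 112 | 83 |

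The upper bound gives the smallest trial in every row.

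**Link workers.** The design effect in the social prescribing arm is 1 + (m − 1) × ICC for m pupils per worker. The article gives neither m nor the ICC. With an assumed ICC of 0.05:

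| m | Social prescribing arm | Averaged over two equal arms |
|---|---|---|
| 5 | 1.20 | 1.10 |
| 13 | 1.60 | 1.30 |
| 20 | 1.95 | 1.48 |

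With 39 pupils in that arm, m = 20 would mean about two workers, which is an extreme across three cities.

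The pilot cannot pin this ICC down. In a simulation with a true ICC of 0.05, the 95% range of estimates was about −0.08 to 0.32 with 3 workers of 13 pupils, and −0.15 to 0.33 with 6 workers of 6. Sizing at 0.32 with m = 13 would imply a design effect of 1 + 12 × 0.32 = 4.84 in that arm.

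**The case against.** The strongest reply is that the direction depends on an analysis model the article does not state. If the full trial averaged the two follow-ups without baseline adjustment, the upper bound would be the cautious one; with adjustment that is so only below r of about 0.25. If 3-month scores were compared unadjusted, r would not matter. This stands as a condition on the point. It does not rescue the plan: averaging does not match the single primary timepoint, and in the unadjusted case the bootstrap would be uninformative for sample size, not protective.

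A reader might infer that the full trial will be sized at the upper bound. The article does not say so. It speaks of exploring the bounds and of refining the sample size, and it also plans point estimates. The power figures above therefore show what would follow from such a step, which the plan does not take.

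A reader might also infer that clustering by link worker has been overlooked altogether. The text does not support that: the article condenses a fuller protocol, and clustering by provider may be handled there or in an analysis plan. What the article does fix is that RQiii estimates within-person ICCs, and these cannot speak to link-worker clustering. It would not help to size the full trial on an upper bound of the link-worker ICC from about 39 pupils, since that bound is too imprecise.

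Finally, one might ask for school and class ICCs from the baseline surveys. Randomisation is by pupil, so the usual cluster-randomisation penalty does not arise, and at the assumed 14% prevalence most of the 780 surveyed pupils lie outside the trial population.

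**Conclusion.** The point holds in a conditional form. For a single 3-month endpoint analysed with baseline adjustment or change scores, the upper bound of the within-person correlation is the favourable bound for sample size, and the lower bound that RQiii needs is not planned. The possible loss is material: from a nominal 90% to between 74% and 81% with 78 pairs, and between 67% and 77% with 43, for the baseline-adjusted analysis. Those figures rest on an assumed r of 0.5, an assumed 90% target and sizing at the upper bound, to which the plan does not commit.

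Severity is moderate. Allocation, outcomes, pilot conduct and the stop-go criteria are unaffected, and the gap can be closed before the full trial is sized. What changes is the conclusion that RQiii can support.

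**What to change.** Replace the bootstrap clause in Data analysis, RQiii, with: *For the baseline-to-3-month within-person correlation we will report bootstrap lower and upper bounds (resampling pupils) and use the lower bound as the cautious value for the full-trial sample size with baseline adjustment.*

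Add: *Because link workers serve only the social prescribing arm, we will report the link-worker ICC descriptively and size the full trial over a range of assumed link-worker ICCs, not on the upper bound of the pilot estimate.*

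The cost is wording only. One bootstrap run yields both bounds, and no new outcome data are needed; the link-worker ICC needs a record of which worker saw each pupil. The downside is that the full-trial sample size may turn out less favourable.
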